## Abstract

**Background:**

Vasculitides comprise a group of rare diseases which affect less than 5 in 10.000 individuals. Most types of vasculitis can become organ- and life-threatening and are characterized by chronicity, high morbidity and relapses, altogether resulting in significant morbidity and mortality. Previous studies have been either monocentric or mainly retrospective – studies with a prospective design mostly consisted of rather small cohorts of 100 to 200 patients.

The aim of the Joint Vasculitis Registry in German-speaking countries (GeVas) is to record all patients who have been recently diagnosed with vasculitis or who have changed their treatment due to a relapse (inception cohort). In GeVas, data are collected prospectively in a multicenter design in Germany, Austria and Switzerland. By this approach, courses of vasculitis and their outcomes can be monitored over an extended period.

**Methods:**

GeVas is a prospective, web-based, multicenter, clinician-driven registry for the documentation of organ manifestations, damage, long-term progress and other outcomes of various types of vasculitis. The registry started recruiting in June 2019. As of October 2020, 14 centers have been initiated and started recruiting patients in Germany. Involvement of sites in Austria and the German-speaking counties of Switzerland is scheduled in the near future.

**Discussion:**

In June 2019, we successfully established a prospective multicenter vasculitis registry being the first of its kind in German-speaking countries. The participating centers are currently recruiting, and systematic analysis of long-term vasculitis outcomes is expected in the ensuing period.

**Trial registration:**

German Clinical Trials Register (Deutsches Register Klinischer Studien): DRKS00011866. Registered 10 May 2019.

## Background

Vasculitides are rare diseases affecting less than 5 in 10.000 people. In general, the vast majority of vasculitides cannot be cured. Thus, they are characterized by chronicity, high morbidity, mortality, and a high tendency for relapse. Most of them are potentially organ- and life-threatening.

In contrast to clinical trials that include selected patient subtypes and often have a short follow up, cohort or registry studies provide important insight on disease presentation and long-term outcomes in a broad and representative population of patients. The significance of most of the earlier cohort studies in vasculitis is limited by various methodological shortcomings such as monocentric patient recruitment, retrospective design and limited number of outcome parameters [1–6]. Furthermore, small cohort studies of no more than 100 to 200 patients have been conducted following response to immunosuppressive therapies with limited follow-up over time. Results of these studies were subsequently supported by follow-up studies with a narrow thematic focus [7–13]. The incidence and prevalence of various types of vasculitis in local regions were calculated based on data of particular university and reference centers [14–16]. In contrast to registry-based data, these studies do not support conclusions regarding initial and cumulative organ involvement, organ damage, long-term progress, and outcomes in various types of vasculitis [17].

Therefore, there is a persistent need for registries documenting disease manifestations and courses, treatment, comorbidities, and long-term outcomes of vasculitis patients in a standardized, multicenter, and prospective manner. Through establishing a registry in German-speaking countries, these rare diseases will be systematically and prospectively recorded for the first time in this European region, thereby enabling the standardized documentation of disease outcomes under the supervision of physicians specialized in vasculitis patient care over an extended period. Furthermore, it is possible to perform comparative analyses on a much larger scale than is possible in monocentric studies.

These data will specifically shed light on how guidelines and standards of treatment are implemented in local centers dealing with the treatment of vasculitis patients, and thus provide insight into the current state of medical care. Analyzing characteristics of the diseases and their outcomes will also be relevant in devising hypotheses and treatment objectives for new treatments for investigator-initiated clinical trials (IITs). Data from the registry may also serve as a basis for identifying needs for improving the structure of healthcare with regard to the specific needs of vasculitis patients in German-speaking countries. Lastly, GeVas will facilitate comparative analyses with other European vasculitis registries.

Here, we report the protocol, methodology, and status of this registry.

## Methods

### Objectives

To record all patients who have been recently diagnosed with systemic or single-organ vasculitides according to the Chapel Hill Consensus Conference (CHCC) nomenclature and definitions, or who have changed their treatment due to a relapse, in a prospective, web-based, clinician-driven, transregional, multicenter registry, and to document long-term disease outcomes in a standardized and systematic manner.

### Trial design

Prospective, web-based, multicenter disease registry.

### Study setting

This registry study is conducted at in- and out-patient care centers involved in the management of vasculitis patients (licensed medical specialists, specialized out-patient departments and wards of secondary and tertiary care facilities) in Germany, Austria and Switzerland. It is intended to include as many centers specialized in vasculitis care and treatment as possible in order to achieve a nationwide coverage of the target patient population. Such centers take care of patients with vasculitis on a regular basis and participate in vasculitis research and/or clinical trials. After obtaining appropriate ethics approvals, the study started by successively initiating centers in Germany. Centers in Austria and German-speaking parts of Switzerland will follow and join the registry.

### Eligibility criteria

Patients with any form of systemic or single-organ vasculitis as defined by the CHCC nomenclature and definitions are included [18]. Patients are registered if they have been newly diagnosed with the disease no more than 6 months before the first visit or if they have had a relapse with change of immunosuppression. Due to the lack of current diagnostic criteria for classifying vasculitis, the following criteria are used for inclusion of patients into the registry [18, 19]: Classification criteria employed in national and international studies, i.e. the American College of Rheumatology Classification Criteria, the nomenclature and definitions of the Chapel Hill Consensus Conference, and the MIRRA criteria for eosinophilic granulomatosis with polyangiitis (EGPA) [18–20]. Moreover, anti-neutrophil cytoplasmic autoantibody-associated vasculitis (AAV) and polyarteritis nodosa can be classified into the respective category using clinical surrogate endpoints following the European Medicines Agency (EMA) algorithm I case histological confirmation of the diagnosis is not possible [21].

Table 1 shows the vasculitis entities eligible to be included in this registry.

**Table 1 Tab1:** Vasculitis entities eligible for inclusion in the GeVas registry

Vasculitis entities	
**1. Large vessel vasculitis**	
• Giant Cell Arteritis • Takayasu Arteritis	
**2. Medium size vessel vasculitis**	
• Polyarteritis nodosa • Kawasaki disease	
**3. Small vessel vasculitis**	
**ANCA-associated vasculitides**	
• Microscopic Polyangiitis • Granulomatosis with Polyangiitis • Eosinophilic Granulomatosis with Polyangiitis	
**Immune complex vasculitis**	
• Anti-GBM(glomerular basement membrane) disease • Cryoglobulinemic vasculitis • IgA vasculitis • Hypocomplementemic urticarial vasculitis (Anti-C1q vasculitis)	
**4. Variable Vessel Vasculitis**	
• Behcet’s disease • Cogan’s Syndrome	
**5. Single Organ Vasculitis**	
• Cutaneous (leukocytoclastic) small vessel vasculitis • Cutaneous arteritis • Primary central nervous system vasculitis • Isolated aortitis • Others	
**6. Vasculitis associated with systemic disease**	
• Lupus vasculitis • Rheumatoid vasculitis • Sarcoid vasculitis • Others	
**7. Vasculitis associated with probable etiology**	
• Hepatitis C virus-associated cryoglobulinemic vasculitis • Hepatitis B virus-associated polyarteritis nodosa • Syphilis-associated vasculitis • Drug-associated immune complex vasculitis • Drug-associated ANCA-associated vasculitis • Cancer-associated vasculitis • Others	

### Interventions

Not applicable. This registry is purely observational in nature, and relies on the documentation of routine data only. Hence, no study-specific interventions are performed.

### Outcomes

The outcomes assessed in this registry are listed in Table 2. An explicit distinction between primary and secondary outcomes is not made, but a list of equivalent outcomes has been defined.

**Table 2 Tab2:** List of outcomes for the GeVas registry

Outcomes	
Demography / Consent	
Initial manifestation / Relapse as defined by EULAR guidelines / Change of treatment	
Comorbidity as outlined in the eCRF during initial manifestation and over the course of disease progression as defined by EULAR guidelines (e.g. diabetes, hypertension, atherosclerotic vasculopathy, osteoporosis)	
Vasculitis entity and formal diagnosis	
Disease activity (as defined in 25)	
Clinical manifestations related to active vasculitis features related to active vasculitis features (e.g. general symptoms, eyes, ENT, lung/chest, renal symptoms, PNS/CNS features etc.)	
Laboratory tests e.g. CRP, ANCA etc.	
Dialysis yes / no // renal transplantation yes / no	
Treatment and response to immunosuppressive therapy (as defined in 25)	
Frequency and types of infectious complications such as pneumonia, urinary tract infections	
Occurrence of comorbidity during disease progression	
Cancer yes/no	
Pregnancy yes/no	
Death incl. Date and cause of death	
BVAS Score / BVAS items (BVAS: Birmingham Vasculitis Activity Score)	
VDI Score / VDI items (VDI: Vasculitis Damage Score)	

### Participant timeline

The visit schedule includes a baseline visit at initial registration (visit 1), at which the diagnosis and the introduction of remission-inducing treatment is documented. A second visit is scheduled after 3 ± 2 months, and a third after 6 ± 3 months, in order to document the switch from remission-inducing to remission-maintaining treatment usually achieved after 3–6 months. Afterwards, visits are scheduled at intervals of 6 months in order to monitor treatment regularly. This visit schedule meets the standard procedures for managing vasculitis patients and is in accordance with the proposed European Vasculitis Society (EUVAS) recommendations for national registries currently undergoing further specification [22–25]. In case of new relapse, complications or other incidents occurring between two visits, these can be entered as unscheduled visit in between or at the next follow-up visit. Registered patients will be followed up for at least 36 months after initial diagnosis; however, this period can be extended.

### Sample size

The number of patients to be included into this registry is not based on a formal sample size calculation, as the purpose of this registry is to obtain an exhaustive documentation of patients with a recent onset or relapse of vasculitis. Given an incidence of 100–200 per 10^6^ inhabitants per year and a prevalence of 400–1.000 per 10^6^ inhabitants for the group of vasculitides [3, 4, 26, 27], it is estimated that approximately 1–5 patients per month will be enrolled into the registry by each center. The period for registering patients, as well as the number of patients, is not limited to ensure a description of the long-term course of the disease that is as accurate and comprehensive as possible.

### Recruitment

All patients with a newly diagnosed vasculitis, or with a treatment change due to relapse, will be screened for inclusion into the registry at the respective study site. If a patient is eligible, she or he will be informed about the study and asked for written informed consent. As vasculitis patients are usually cared for by specialized consulting physicians or specialized out-patient departments or hospitals, we aim to include as many of these specialized centers as possible into the registry.

Since its initiation in June 2019, our registry has included 14 sites in Germany and documented more than 100 vasculitis patients. GeVas is driven by an active and quickly growing research community. Further sites across Germany, Austria and Switzerland are being recruited. As of November 2020, more than 20 additional sites in the three countries have expressed their interest to participate.

### Data collection methods and data management

Data collection takes place via a web-based, electronic case report form (eCRF) in RDE-LIGHT (RDE = Remote Data Entry), a system based on HTML and Javascript that has been developed in-house by the Clinical Trials Unit (CTU) of the Medical Center, University of Freiburg. The data center of the Medical Center, University of Freiburg, runs the system (software, MySQL-database and web server), which is subject to strict access controls. Data transfer is encrypted (https, SSL certificate). RDE-LIGHT is validated according to GAMP5 and is GCP-compliant, e.g. presence of an audit trail. Furthermore, all data is backed up on a daily basis and archived regularly. User account management is controlled centrally by the CTU in Freiburg. Appropriate technical and organizational measures are implemented to comply with EU General Data Protection Regulation (GDPR) and other applicable data protection legislation.

The participating centers receive a video tutorial and a manual in print for accessing and using the eCRF. The participating centers enter the appropriate routine data from the medical records of the patients into the eCRF via a standard web browser. The eCRF is organized into specific sections (demographics, vasculitis entity, clinical features, immunosuppressive treatment, etc.) which correspond to the list of outcomes and in which the respective parameters are recorded in a standardized form. Participating centers can view their own data and export them in DSV format (delimiter-separated values).

Data recording is in pseudonymous form only, that is, each patient is assigned a patient identification code in the registry before any data entry takes place. The patient ID code is assigned by the respective participating site and can be decoded by this site only.

### Statistical methods

The primary objective of the study is to register all patients who have been diagnosed recently with vasculitis or who have changed their treatment due to relapse, and to document their long-term disease course. The statistical analysis is therefore solely descriptive.

Initially, the quality of data will be described, i.e. the number of documented patients and the completeness of the data. Demographic information, incidences of different types of vasculitis, organ damage, comorbidity and additional disease-specific symptoms upon initial diagnosis will be analyzed in order to describe the patient cohort. Time-to-event endpoints, such as overall survival time, time to treatment response and time to relapse, are estimated and described using Kaplan-Meier methodology.

Beside the median, the corresponding 95% confidence intervals for the respective time to event will be presented. Continuous variables will be presented with number of observations, mean, standard deviation, 25% quantile, median, 75% quantile as well as minimum and maximum. Categorical variables will be presented by absolute and relative frequencies.

Analyses will be performed for all patients. Depending on the research question and the number of available observations, subgroup analyses by type of vasculitis and center may be performed in addition.

The first analysis will be conducted 12 months after the registration of the first patient and yearly analyses are envisaged. Analyses relating to specific research questions can be conducted as required.

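### Kaplan-Meier is assigned to time to relapse and time to treatment response although death precludes both; if deaths are censored, relapse and response are overstated and the medians come too early

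*Protocol article*

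**What the plan says.** The Statistical methods section of the protocol article names one estimator for three endpoints: "Time-to-event endpoints, such as overall survival time, time to treatment response and time to relapse, are estimated and described using Kaplan-Meier methodology". The numerical summary follows: "Beside the median, the corresponding 95% confidence intervals for the respective time to event will be presented". The same section limits the purpose: "The statistical analysis is therefore solely descriptive".

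Three other places bear on the point. The Background says of these diseases that "they are characterized by chronicity, high morbidity, mortality, and a high tendency for relapse", without giving a rate. Table 2 in the Outcomes section lists "Death incl. Date and cause of death" among the recorded items. The Participant timeline says: "Registered patients will be followed up for at least 36 months after initial diagnosis; however, this period can be extended".

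The article does not say how a death enters the relapse and response analyses, and it names no method for competing events. For the definitions of relapse and response, Table 2 refers to outside sources.

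**The concern.** Overall survival is listed as its own endpoint, next to time to relapse and time to treatment response. The natural reading is that the last two count only relapse and only response. A patient who dies without the event then has to leave the Kaplan-Meier risk set as censored. Censoring treats that patient as still able to relapse or respond later at the same rate as those who remain. The resulting curve describes a population in which nobody dies. It does not give the share of registry patients who actually relapse or respond.

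In a descriptive registry the estimate is itself the product. The Background wants the results to shape hypotheses and treatment goals for new trials, to inform care structures and to allow comparison with other registries. The distortion grows with mortality and with length of follow-up. If results are broken down by vasculitis type, which the plan allows but does not promise, types with different mortality would be affected to different degrees.

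**Working it through.** **Inputs.** The article states no relapse, response or death rate, so there is no figure of its own to reproduce. All rates below are assumptions, and ranges are shown. Constant, independent hazards are assumed: `r` for relapse (or response) and `d` for death. Each hazard is set from a net probability `p` by time `T0`, as `-ln(1 - p)/T0`.

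**Formulas.**
- One minus Kaplan-Meier with deaths censored: `1 - exp(-r*T)`.
- Cumulative incidence, the target of Aalen-Johansen: `r/(r + d) * (1 - exp(-(r + d)*T))`.

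The first is never below the second, so the direction is fixed and only the size depends on the rates.

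**One case in full.** Take net relapse of 40% and mortality of 10% by 36 months.
- `r = -ln(0.6)/3 = 0.1703` per year and `d = -ln(0.9)/3 = 0.0351` per year.
- One minus Kaplan-Meier at 3 years is 40.0%.
- Cumulative incidence is `0.1703/0.2054 * (1 - 0.6*0.9) = 0.829 * 0.46 = 38.1%`.
- The overstatement is 1.9 points.
- The Kaplan-Meier median is `ln 2/0.1703 = 4.07` years. The cumulative incidence reaches 50% at `-ln(1 - 0.5/0.829)/0.2054 = 4.50` years.

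**Overstatement of relapse at 36 months, in percentage points, by assumed 36-month mortality.**

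| Net relapse by 36 months | 5% | 10% | 20% | 30% |
|---|---|---|---|---|
| 20% | 0.5 | 1.0 | 2.0 | 3.1 |
| 40% | 0.9 | 1.9 | 3.8 | 5.8 |
| 60% | 1.3 | 2.6 | 5.3 | 8.2 |

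**Other time points.** With the same hazards, net relapse of 20–60% and 36-month mortality of 3–30%, the overstatement is 0.0–1.4 points at 12 months, 0.3–8.2 at 36 months and 0.7–14.9 at 60 months.

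**Response at 6 months.** With net response of 60–90% and 2–15% dead by 6 months, the overstatement is 0.5–4.6 points. For 80% response and 5% deaths, `r = -ln(0.2)/0.5 = 3.219` and `d = -ln(0.95)/0.5 = 0.103` per year. One minus Kaplan-Meier is 80.0% and the cumulative incidence is 78.5%. The median hardly moves: `ln 2/3.219 = 0.215` years against `-ln(1 - 0.5/0.969)/3.321 = 0.218` years.

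**Median overall survival.** With a constant hazard, survival falls to 50% by `T` years only if annual mortality is `1 - 0.5^(1/T)`: 50% for 1 year, 20.6% for 3 years, 12.9% for 5 years and 6.7% for 10 years. An unreached median is therefore likely at the first analyses. Later it depends on mortality and on how far follow-up is extended.

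**The case against.** The strongest reply is that the bias is inferred. No sentence says that deaths are censored. Kaplan-Meier is valid where death counts as an event, as in relapse-free survival, and a condensed article may leave event and censoring rules to a fuller plan. The plan also promises medians, not relapse or response probabilities, and does so in a purely descriptive setting with no test or decision rule.

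Part of this stands. The statement must be conditional: the figures are too high if deaths are censored. What does not stand is that the choice was left open. The article itself fixes the estimator, lists overall survival separately and presents neither endpoint as a composite, so censoring is the natural reading. The medians are affected as well, since they come too early.

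A second reply is that the size is unknown and may be trivial. This stands for short follow-up and low mortality. A reader might take the Background as saying that mortality is high and so expect a large bias. The text names mortality as a feature without a rate, so nothing in the article selects the upper end of the ranges.

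A reader might also infer that the planned median is a defect because median overall survival will often not be reached. The article does not support that. An unreached median is an honest result, the confidence interval and the Kaplan-Meier curve remain usable, and 36 months is a minimum that can be extended.

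**Conclusion.** The point holds in conditional form and is moderate: it should be fixed, but it does not undermine the registry. If deaths are censored, one minus Kaplan-Meier overstates relapse and response, and the reported median is too early.

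Under the assumed constant, independent hazards, the overstatement of relapse is negligible at 12 months. It is about 1–5 points at 36 months with 5–20% mortality by then, and larger with higher mortality or longer follow-up. For response at 6 months it is 0.5–4.6 points, with the upper end needing 15% dead by that time. The direction does not depend on these assumptions, but the size does, and the article gives no rate that would settle it. That median overall survival may go unreached at early analyses is a matter of reporting, not an error.

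**What to change.** In Statistical methods, keep Kaplan-Meier for overall survival. For time to relapse and time to treatment response, state that death is a competing event and that the cumulative incidence is estimated by Aalen-Johansen with 95% confidence intervals. If a composite such as relapse-free survival is what is meant, say so and name it that way; Kaplan-Meier is then appropriate.

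Optionally, report all time-to-event estimates with 95% confidence intervals at fixed times such as 12, 24 and 36 months, and give the median where it is reached.

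The cost is a sentence or two of text and a little extra analysis in standard software. Dates of death are already recorded, so no new data are needed. Reported relapse and response figures will be slightly lower, and the time by which half the patients have had the event will be later or may not be reached.
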